#### Safety evaluation

2.9.4

According to the study group and the control group, the number and proportion of abnormal cases before and after treatment are described respectively. AEs are described by the number and incidence of AEs, and the proportion is tested by continuous correction χ^2^ test or Fisher's exact probability method. At the same time, depict the specific manifestations, degree and relationship with the study drug of all AEs occurred in each group of cases in detail.

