### Study design

2.1

This is a single-center, prospective randomized trial that will enroll 64 SCAD patients with normal FFR and CMVD. The protocol has been approved by the Ethics Committee of Sir Run Run Show Hospital Affiliated to Zhejiang University School of Medicine (No.20200423–36). Participants who meet the eligibility criteria will be enrolled and randomly allocated to study group and control group in a 1:1 fashion. On the basis of conventional drug treatment, the former will receive STDP while the latter will not. The follow-up period of the subjects was 12 months, and clinical follow-up will be conducted before discharge, 30 days, 3 months, 6 months, and 12 months after procedure to complete the detection of relevant indicators. The study flow chart is shown in Figure 1.

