**Figure 1 F1:**
[figure not shown]
Study flow chart.

Corresponding parameters shown in Table 1 including laboratory tests and other indicators will be recorded or assessed at each follow-up by the responsible physician.

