#### Safety endpoints

2.7.2

All parameters related to the participants’ safety including vital signs, physical examination, hematologic test, biochemical test, and judged cardiovascular events will be documented on the CRF at every visit. Any adverse events (AEs) that occur after taking test drug, regardless of the severity and whether they are related to the test drug, will be documented on the CRF and reported in a timely manner. If the AE is severe and related to STDP, the participant will be withdrawn from the study, and the follow-up and appropriate treatment will be provided to them.

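### Section 2.9.4 counts abnormal safety results before and after treatment in each arm; these totals do not identify new abnormalities, and the post-treatment time point is not fixed

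*Protocol article*

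**What the plan says.** All references are to the protocol article.

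- **Data collected.** Section 2.7.2 (Safety endpoints) says that "vital signs, physical examination, hematologic test, biochemical test, and judged cardiovascular events will be documented on the CRF at every visit". Section 2.1 (Study design) gives the schedule: "clinical follow-up will be conducted before discharge, 30 days, 3 months, 6 months, and 12 months after procedure". The text after Figure 1 adds that the Table 1 parameters, "including laboratory tests and other indicators will be recorded or assessed at each follow-up by the responsible physician".
- **Summary of safety parameters.** Section 2.9.4 (Safety evaluation) says that, for the study and control groups, "the number and proportion of abnormal cases before and after treatment are described respectively". It names no visit, does not define abnormal, and mentions no within-participant change.
- **Adverse events (AEs), handled separately.** Section 2.7.2 requires that any AE, "regardless of the severity and whether they are related to the test drug, will be documented on the CRF". Section 2.9.4 then states: "AEs are described by the number and incidence of AEs, and the proportion is tested by continuous correction" chi-square or by Fisher's exact method. It also undertakes to "depict the specific manifestations, degree and relationship with the study drug of all AEs occurred in each group of cases in detail".
- **General description.** Section 2.9.1 lists means, SDs, ranges and quartiles for measurement data, without reference to change within a participant.

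**The concern.** For the routine safety parameters, the question is whether adding STDP makes normal results abnormal. That is a within-participant transition. A before total and an after total discard the pairing: a participant whose result normalises cancels one whose result becomes abnormal, and the two totals can agree while both kinds of change occur.

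The second issue is timing. The data come from several visits, but the summary has two columns and no rule for filling the second. The analyst could take the last value, each visit in turn, the worst value or any abnormal value. These give different tables, and the text does not choose among them in advance.

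At stake is the quality of the safety description in a trial that states safety as an aim (abstract, Discussion paragraph). The efficacy conclusion is not affected.

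**Working it through.** **Plan's own figure.** The documents give no number for safety abnormalities. The only input taken from them is the arm size in section 2.8: 25 per arm with 20% drop-out, 25 / (1 − 0.20) = 31.25, rounded up to 32. All abnormal counts below are assumed for illustration.

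**Step 1: what the totals determine.** Let n participants in an arm be measured at both times, with *a* abnormal before and *b* abnormal after. Let *x* be the number newly abnormal and *r* the number resolved. Then b = a + x − r, with 0 ≤ r ≤ a and 0 ≤ x ≤ n − a. So *x* lies between max(0, b − a) and min(b, n − a).

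| Before, of 32 | After, of 32 | New abnormalities | Normal at baseline | As % of those |
|---|---|---|---|---|
| 6 | 6 | 0 to 6 | 26 | 0% to 23.1% |
| 4 | 4 | 0 to 4 | 28 | 0% to 14.3% |
| 4 | 6 | 2 to 6 | 28 | 7.1% to 21.4% |
| 8 | 8 | 0 to 8 | 24 | 0% to 33.3% |

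If a = 0, then x = b exactly. The ambiguity therefore grows with the number abnormal at baseline and disappears when there are none. These are logical limits, not likely effects.

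**Step 2: what the control arm adds.** With S for the study arm and C for control, b_S − b_C = (a_S − a_C) + (x_S − x_C) − (r_S − r_C). The *a* and *b* terms are reported. If equal numbers resolve in both arms, the difference in new cases is recovered. If they do not, only the net of new and resolved cases is seen. Extreme case: 6 before in both arms, 6 new and 6 resolved on STDP, none of either in control. Both arms show 6/32 after, while new cases are 6/26 = 23.1% against 0/26 = 0%.

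**Step 3: what the time point changes.**

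- *Last visit only.* An abnormality present at just one of the four visits from 30 days to 12 months is seen only if it falls at the last one: 1 in 4 if each visit is equally likely (an assumption).
- *Each visit separately.* A transient abnormality appears at its visit, but the counts are still marginal.
- *Any visit.* Nothing recorded is lost, but *after* then pools several assessments against a single *before*, so the two proportions are not like for like.

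The wording in 2.9.4 fits all three readings.

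**The case against.** The strongest reply has four parts.

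1. **This is detail for an analysis plan that is not shown.** Shift tables and by-visit tables are commonly left there, and a journal article condenses. This lowers the severity. It does not remove the point, because 2.9.4 states a particular summary, and an analysis that followed it literally would produce the marginal table.
2. **Safety is not summarised by these counts alone.** A reader might infer that it is. Section 2.9.4 also plans tested AE incidence and a detailed account of every AE, so a transient abnormality recorded as an AE would be reported. This stands. What is left is that nothing shown requires an abnormal laboratory value to be recorded as an AE, and neither the AE analysis nor the statistics in 2.9.1 show shifts from baseline.
3. **The intermediate visits are not said to be dropped.** A reader might infer from the two-column wording that the 30-day, 3-month and 6-month results are discarded. The text does not say so: every one of those visits comes after treatment has begun. The supportable statement is that the time point is undefined and that loss of transient findings follows on one reading.
4. **Harmed participants are not hidden by withdrawal.** A reader might infer that someone withdrawn for a severe STDP-related AE vanishes from the safety results. Such a participant is counted and described as an AE, and 2.7.2 promises follow-up. The article leaves open only whether that participant's parameter values enter the *after* column.

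In addition, counts are given for both arms, so a net excess on STDP would normally be visible (Step 2). This stands and limits the risk of false reassurance.

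**Conclusion.** The point holds as a low-severity improvement. The stated summary of safety parameters gives marginal counts, which bound but do not identify new abnormalities. With 32 per arm and an assumed 6 abnormal at both times, the bound is 0% to 23.1% of those normal at baseline. The documents do not support saying that the summary can never show new abnormalities: the totals sometimes force a minimum (4 before and 6 after means at least 2), and they are exact when nobody is abnormal at baseline.

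The undefined post-treatment time point is a separate, equally modest gap. The size of either problem depends on baseline abnormality rates and on how long abnormalities last; the documents give neither. The bounds also assume that the same participants are measured at both times. With the 20% drop-out allowed for in 2.8, the before and after columns may rest on different people unless the plan says otherwise. The primary endpoint, the sample size and the AE analysis are unaffected.

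**What to change.** Replace the first sentence of section 2.9.4 with wording such as:

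> For each safety parameter, the number and proportion of participants normal at baseline who have at least one abnormal value at any post-randomisation visit will be given by arm, with the between-arm difference and its 95% confidence interval. A table of shifts from baseline to the worst post-baseline value will be shown by arm. All available values will be used, including those obtained before withdrawal.

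Name the assessment that serves as baseline and state how abnormal is defined for each parameter. Report visits attended by arm, since a participant with fewer visits has fewer chances to show an abnormality. Keep the AE analysis as it stands.

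The cost is analysis wording and table programming. The values are already scheduled at every visit, so no new data, visits or participants are needed.

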#### Primary and secondary endpoints

2.7.1

The primary endpoint is the change of Index of Microcirculatory Resistance (ΔIMR) at 12-month follow-up. The secondary endpoints are major adverse cardiovascular events (MACE, including cardiac death, myocardial infarction, ischemic stroke, unstable angina requiring hospitalization, coronary revascularization) at 12-month follow-up; the change in corrected TIMI frame count (ΔCTFC) after 1-year follow-up; the change in coronary flow reserve (ΔCFR) at 1-year follow-up.

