#### Baseline demographic analysis

2.9.2

Continuous correction χ^2^ test is used for comparison between count data groups. When the theoretical frequency of more than 25% of cells is <5, Fisher's exact probability method is used; comparison between groups of normally distributed measurement data uses group *t* test; for non-normally distributed measurement data, Wilcoxon rank sum test is used for comparison between groups.

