#### Efficacy analysis

2.9.3

Continuous correction χ^2^ test is used for comparison of MACE count treatment groups, paired *t* test is used for comparison of normal distribution measurement data groups; Wilcoxon sign rank is used for comparison of non-normal distribution measurement data groups (Wilcoxon Sign Rank) Test: The method of comparison between groups is the same as the baseline analysis.

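### The planned test for MACE and adverse-event proportions is valid but needlessly conservative; Boschloo's exact test would gain some power at no cost in type I error

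*Protocol article*

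**What the plan says.** Three sections of the protocol article together fix the test for proportions.

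- **2.9.2 Baseline demographic analysis** names the continuity-corrected χ² and its fallback: "When the theoretical frequency of more than 25% of cells is <5, Fisher's exact probability method is used".
- **2.9.3 Efficacy analysis**: "Continuous correction χ^2^ test is used for comparison of MACE count treatment groups". It adds: "The method of comparison between groups is the same as the baseline analysis". On the natural reading, the Fisher fallback therefore carries over to MACE.
- **2.9.4 Safety evaluation**, on adverse events: "and the proportion is tested by continuous correction" χ² or by Fisher's exact test.

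MACE is a secondary endpoint (2.7.1: "The secondary endpoints are major adverse cardiovascular events"). Section 2.8 plans 32 patients per arm from ΔIMR alone, at a one-sided 5% level. The article states no significance level, sidedness, power or expected event rate for MACE or adverse events.

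**The concern.** The continuity correction brings χ² close to Fisher's conditional test. In small samples both have a true type I error well below the nominal level, because few tables are possible once the total number of events is fixed. With 32 per arm, that gap costs power. For MACE, a real benefit is harder to show. For adverse events, a real excess on STDP is more likely to be reported as not statistically significant, which is the less safe direction of error. Conservatism can be defended as the price of a guaranteed error rate. The question is whether another test gives the same guarantee at a lower price.

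**Working it through.** **Inputs**
- 32 per arm, or about 25 evaluable after 20% drop-out (2.8).
- Planned rule: corrected χ², or Fisher when more than 25% of the four expected counts are below 5 (2.9.2 to 2.9.4). Section 2.9.4 does not say when Fisher applies, so the 2.9.2 rule is assumed there.
- *Assumption:* two-sided 5% level.
- *Assumption:* event rates, since none is given. The lower-rate arm was varied from 2% to 50%, and the difference from 5 to 40 points.

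**The plan's own figure.** No size or power is stated for these tests, so only the sample size can be reproduced. n = 2(1.645 + 1.282)² × 6.0² / 5.0² = 24.7, so 25 per arm, using the larger SD for both arms. Then 25 / 0.8 = 31.25, so 32. Both agree with 2.8.

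**Where the fallback applies.** At 32 per arm the expected event count per arm is half the total. Fisher is used with 9 or fewer events (expected 4.5 or less), or 9 or fewer non-events; otherwise the corrected χ² is used. Applying the corrected χ² throughout gives the same sizes and powers to the decimals shown, so the reading of 2.9.4 does not matter here.

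**Method.** Every 2×2 table (a, b) at 32/32 is classed as rejected or not. For rejection set R:
- size(p) = Σ over R of Bin(a; 32, p) × Bin(b; 32, p)
- power(p₁, p₂) = Σ over R of Bin(a; 32, p₁) × Bin(b; 32, p₂)

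Boschloo's test rejects when the Fisher p-value is at or below a cut-off c, the largest value that keeps the maximum of size(p) over all p at or below 5%. At 32/32, c = 0.0746.

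**True size, 32 per arm**

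| Event rate | Planned rule | Boschloo |
|---|---|---|
| 5% | 0.2% | 0.9% |
| 10% | 1.1% | 2.5% |
| 20% | 2.3% | 3.9% |
| 30% | 2.4% | 4.5% |
| 50% | 3.3% | 3.8% |
| Maximum over all rates | 3.3% | 4.7% |

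**Power, 32 per arm, assumed rates**

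| Rates | Planned rule | Fisher alone | Boschloo |
|---|---|---|---|
| 5% vs 10% | 2.3% | 2.3% | 5.4% |
| 5% vs 20% | 27.6% | 27.6% | 36.7% |
| 10% vs 20% | 10.9% | 10.9% | 15.1% |
| 10% vs 30% | 40.3% | 41.1% | 48.5% |
| 20% vs 40% | 30.7% | 32.9% | 40.0% |
| 40% vs 60% | 29.8% | 29.8% | 31.7% |

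Over the whole assumed range, Boschloo gains 0.6 points (2% vs 42%) to 14.3 points (2% vs 17%). Fisher alone gains 0 to 2.7 points.

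**Dominance.** At 32/32 Boschloo rejects every table that the planned rule rejects, plus 36 more; at 25/25, all of them plus 24 more. A larger rejection set means higher power at every pair of rates strictly between 0 and 1, so the direction of the result needs no assumed rate. It also held at 26/26, 28/36, 27/37, 24/28 and 30/34, with 24 to 42 extra tables.

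**Example.** For 0 of 32 versus 5 of 32, the plan uses Fisher: p = 2 × C(32,5) / C(64,5) = 2 × 201,376 / 7,624,512 = 0.053. For 1 versus 7, p = 2 × [32 × C(32,7) + C(32,8)] / C(64,8) = 236,451,384 / 4,426,165,368 = 0.053. Neither is significant under the plan. Both lie below c = 0.0746, so Boschloo rejects both.

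**Other arm sizes.** For 10% vs 30%, planned rule and Boschloo give 30.5% and 38.6% at 25 per arm, and 39% and 49% at 28/36 (simple randomisation can leave the arms unequal). The small recovery from Fisher alone is a result for equal arms; with unequal arms it can be larger.

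**The case against.** The strongest reply is that nothing here is wrong. A corrected χ² with Fisher for sparse tables is conventional and controls type I error. It is applied to outcomes on which the trial is not sized and for which no power is claimed. That stands, and it sets the severity. It does not remove the point, because Boschloo controls type I error too, so validity cannot be the reason to prefer the planned rule.

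Four stronger readings are tempting, and none is supported.

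- *Any exact test would recover the power.* Fisher's test is exact, is the plan's own fallback, and recovers 0 to 2.7 points at 32 per arm and nothing at 25. The gain needs an unconditional test.
- *The loss is a fixed figure, say 6 to 10 points.* The article gives no event rates and no level for these tests. For 5% vs 10% and 10% vs 20% the gain is 3 to 4 points, and power is about 15% or less either way. At 27/37, 5% vs 10% gains only 0.3 points.
- *The alternative would run at 5%.* Boschloo is also well below 5% when events are rare: 0.9% at a 5% rate.
- *A safety signal would be hidden.* Section 2.9.4 also calls for the number and incidence of adverse events, and for the manifestations, degree and relationship to study drug of each one. An excess would be visible whatever the p-value.

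Some statisticians also prefer Fisher's test on principle, because it conditions on the total number of events. That is a legitimate preference, but the article does not argue it.

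**Conclusion.** The point holds as a low-severity efficiency improvement, not as an error. Assuming a two-sided 5% level, the planned rule has a true size of at most 3.3% at 32 per arm. Boschloo's test, with maximum size 4.7%, dominates it, so there is no trade between validity and power against that test. Dominance was shown by full enumeration at each arm size listed and does not depend on event rates. The size of the gain does: about 1 to 14 points at 32 per arm over the assumed rates, and small where both rates are low and close together. The primary ΔIMR analysis and the sample size are unaffected.

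**What to change.** In 2.9.3 and 2.9.4, compare the proportions of patients with MACE, and with adverse events, by Boschloo's unconditional exact test. State the level and sidedness, and report the risk difference with a score-based 95% confidence interval. This also removes the switch between tests that depends on expected counts. The mid-p version of Fisher's test should not be substituted if a guaranteed 5% is wanted: its maximum size just passes 5% at 32/32 (5.001%) and reaches 5.14% at 24/28.

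The cost is a wording change, and standard software runs the test. The small downside is a test name that fewer readers will know.

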**Discussion::**

The present study will be the first randomized control study to evaluate the efficacy and safety of STDP on SCAD patients, CAD with normal FFR and CMVD, which will provide a broader idea and more experimental basis for improving the treatment of CMVD.

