### Sample size

2.8

The sample size is calculated according to the main evaluation index ΔIMR at 12-month follow-up. Based on previous study, the level of ΔIMR is hypothesized to be 15.0 ± 6.0 and 10.0 ± 4.0 in study group and control group, respectively. When the calculation is performed using 90% power, and a 5% significance level (one-sided test), random distribution ratio is 1:1, the minimum number of members in each group is 25. Considering a drop-out rate of 20%, the needed sample size is approximately 32 participants for each group. Therefore, a total of 64 participants are needed for the present study.

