STDP is a formulate traditional Chinese Medicine widely used to treating clinical cardiovascular disease, especially in stable angina pectoris in China and South Asia.^[13–16]^ It is a complex herb formula, ultra performance liquid chromatography coupled with triple-quadrupole tandem mass spectrometry (UPLC QqQ-MS/MS) Quantitative Analysis revealed 13 major chemical constituents in STDP,^[17]^ which has the functions of dilating blood vessels, anti-inflammatory and reducing endothelial damage. Previous studies have revealed that STDP has a significant improvement on myocardial ischemia. In the rat model of acute myocardial ischemia induced by Pituitrin, the application of STDP can prevent ST segment elevation, reduce whole blood viscosity, and serum CK-MB and LDH levels were lower, result in down-regulation of Bax expression and up-regulation of Bcl-2 expression in myocardial tissue.^[18]^ At the same time, a study explored the probable mechanism of STDP to protect myocardial ischemia, which discovered that STDP protected against the ISO-induced myocardial ischemic injury via an ERK1/2 signaling pathway, thereby providing a mechanism to support clinical applications of STDP as treatment for ischemic heart disease.^[19]^ In addition, STDP can also alleviate atherosclerotic lesions, which has been confirmed in ApoE-deficient mouse models.^[20]^ Related pharmacological studies have proposed that STDP can protect endothelial cells from atherosclerotic lesions by decreasing levels of endothelin-1 (ET-1), C reactive protein (CRP), tumor necrosis factor-α (TNF-α) and increasing levels of nitrogen oxide (NO) in the blood,^[21]^ indicating its potential effect on the pathophysiology of atherosclerosis, including lipid regulation, fibrosis, inflammation and oxidative stress.^[22]^

As mentioned above, the effect of STDP on improving the coronary microvascular function is worthy of expectation. Our study will be the first randomized controlled study to investigate the effect of STDP in SCAD patients with normal FFR and CMVD. By assessing clinical efficacy as well as safety of CMVD, the data obtained may guide STDP use in CMVD.

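### Section 2.9.4 compares adverse-event proportions only by a conservative significance test; a risk difference with an interval would serve the trial's safety aim better

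*Protocol article*

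**What the plan says.** Section 2.9.4 (Safety evaluation) plans three things: the number and proportion of abnormal cases before and after treatment in each arm; the number and incidence of AEs; and a case-by-case account of each AE, its degree and its relationship to the study drug. For the comparison between arms it says that "the proportion is tested by continuous correction χ^2^ test or Fisher's exact probability method". It names no effect measure or interval, and no significance level or sidedness.

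Section 2.9.2 gives, for baseline data, the rule for choosing between the two tests: Fisher when more than 25% of cells have an expected count below 5, otherwise the continuity-corrected χ².

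Section 2.8 bases the size of the trial on efficacy: "The sample size is calculated according to the main evaluation index ΔIMR at 12-month follow-up". It works "using 90% power, and a 5% significance level (one-sided test), random distribution ratio is 1:1", finds that "the minimum number of members in each group is 25", and after allowing for drop-out says that "the needed sample size is approximately 32 participants for each group".

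The Discussion paragraph of the abstract presents the trial as "the first randomized control study to evaluate the efficacy and safety of STDP on SCAD patients". The main Discussion closes with: "By assessing clinical efficacy as well as safety of CMVD, the data obtained may guide STDP use in CMVD".

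**The concern.** Evaluating safety means asking how much harm the data leave possible. A significance test of AE proportions answers a different question, and both named tests are conservative when counts are small. In an efficacy comparison, conservatism guards against a false claim of benefit. In a harm comparison it works the other way and makes a real excess harder to flag.

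With 32 per arm and uncommon events, a non-significant result is likely even if STDP raises the AE rate several-fold. A reader given only counts and a p value is not told how large an excess the data still allow.

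**Working it through.** **Inputs from the documents.** 25 per arm before and 32 per arm after the 20% drop-out allowance (section 2.8); test choice (section 2.9.4); rule for choosing Fisher (section 2.9.2, applied here to AEs).

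**Assumptions.** Two-sided 5%, because no level is stated for safety. All AE rates below, because the article gives none.

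**1. The plan's own figure.** Taking the larger SD, 6.0, as common to both arms and a difference of 15.0 − 10.0 = 5:

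n = 2 × (1.645 + 1.282)² × 6² / 5² = 2 × 8.57 × 1.44 ≈ 24.7, so 25 per arm. Then 25 / 0.8 = 31.25, so 32 per arm and 64 in total.

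The stated size reproduces, and no safety quantity enters it.

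**2. Rejection rate with no true difference.** For every pair of counts (x, y) with 32 per arm, apply the planned test and sum Bin(x; 32, p) × Bin(y; 32, p) over the tables with p value below 0.05.

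| AE rate in both arms | Planned procedure | Uncorrected χ² |
|---|---|---|
| 5% | 0.2% | 3.2% |
| 10% | 1.1% | 5.6% |
| 20% | 2.3% | 5.1% |

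The nominal level is 5%. Even at a 20% AE rate the planned procedure runs at less than half of it.

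**3. Chance of missing a fourfold excess.** Same enumeration with different rates in the two arms; the miss rate is 1 − power.

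| Control vs STDP (assumed) | Missed, 32 per arm | Missed, 25 per arm |
|---|---|---|
| 2% vs 8% | 97.8% | 99.2% |
| 5% vs 20% | 72.4% | 80.2% |
| 10% vs 40% | 26.8% | 40.9% |
| 15% vs 60% | 4.4% | 10.8% |

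The result depends almost wholly on the control rate. The level matters too: a one-sided 5% Fisher test at 32 per arm misses 5% vs 20% about 60% of the time.

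**4. Power given up through the choice of test (32 per arm).** Planned procedure against uncorrected χ²:

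- 5% vs 20%: 27.6% against 48.0%
- 10% vs 25%: 23.7% against 35.7%
- 10% vs 30%: 40.3% against 53.2%
- 20% vs 40%: 30.7% against 42.4%

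The loss is 12 to 20 percentage points.

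**5. What the p value leaves out: 6/32 on STDP against 2/32 on control.** The expected counts are 4, 4, 28 and 28. Two of four cells (50%) are below 5, so the rule selects Fisher: p = 0.26.

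The risk difference is 0.1875 − 0.0625 = 0.125. The Wilson 95% limits are 0.089 to 0.353 for 6/32 and 0.017 to 0.201 for 2/32. Newcombe's limits are then:

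- lower: 0.125 − √[(0.1875 − 0.089)² + (0.201 − 0.0625)²] = −0.045
- upper: 0.125 + √[(0.353 − 0.1875)² + (0.0625 − 0.017)²] = +0.297

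The non-significant result is compatible with an excess of almost 30 percentage points.

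**6. No events in an arm.** The exact one-sided 95% upper bound for 0/32 is 1 − 0.05^(1/32) = 8.9%.

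**The case against.** The strongest reply is that the article never plans to read a non-significant test as proof of safety. It speaks of evaluating and assessing, and the test stands beside full descriptive reporting from which a reader could compute an interval. This stands. A reader might infer from the pairing of a safety aim with a significance test that p > 0.05 will be reported as safe, but no sentence says so. The stated aim therefore needs no rewording.

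Second, a reader might take 72% as the plan's general failure rate for a fourfold excess. The documents do not support that. It belongs to an assumed 5% vs 20%. Section 2.7.2 records AEs of any severity and causality over a 12-month trial, so nothing fixes the any-AE rate at 5%. At 10% vs 40% the planned test has about 73% power.

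Third, calling this the trial's only between-arm safety comparison would go too far. Section 2.7.2 lists judged cardiovascular events among the safety parameters, and section 2.9.3 compares MACE between arms, also by continuity-corrected χ². The statement holds for AE proportions within section 2.9.4.

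Fourth, both tests are valid and standard for small counts, and a condensed article may leave intervals to a fuller plan. That is fair, so the absence of an interval is not in itself an error. But the article does not leave the AE comparison open: it names the method. Whether that method suits a harm question can be judged from what is written.

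**Conclusion.** The point holds as a cheap improvement to a stated analysis choice; the plan contains no error or contradiction here. The AE comparison fixed in section 2.9.4 is conservative in the direction that is unhelpful for harm, with actual rejection rates of 0.2% to 2.3% for AE rates of 5% to 20%, and its output does not bound the excess.

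How often a real excess would be missed cannot be stated as one figure. For a fourfold excess at 32 per arm it runs from about 98% (2% vs 8%) to 4% (15% vs 60%). The concern therefore bites for uncommon events and largely disappears for very large excesses over common ones. These figures rest on the assumed two-sided 5% level, the assumed AE rates, and the section 2.9.2 rule carried over to AEs.

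**What to change.** In section 2.9.4:

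- Make the between-arm risk difference with a 95% Newcombe or Miettinen-Nurminen interval the main comparison, for participants with any AE and participants with any serious AE.
- For event categories with no cases in an arm, give the exact upper bound (8.9%, one-sided 95%, for 0/32).
- Keep any χ² or Fisher p value as supplementary.

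The descriptive listing stays as planned. The cost is a revised paragraph and a few table columns, with no new data or participants. The downside is that the intervals will be wide, so the safety statement will be more cautious.
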